## Abstract

**Background:**

Physical activity may reverse frailty in the elderly, but we encounter barriers to the implementation of exercise programs in this population. Our main aim is to evaluate the effect of a multicomponent physical activity program, versus regular medical practice, on reverting pre-frailty status among the elderly, 12 months post-intervention.

**Methods:**

Randomized parallel group multicenter clinical trial located in primary care setting, among non-dependent and pre-frail patients > 70 years old, including 190 patients (95 intervention, 95 control group). Intervention: Multicomponent physical activity program (MEFAP, for its acronym in Spanish) with twelve 1.5 h-weekly sessions comprised of: 1. Informative session; 2. Exercises for improving aerobic resistance, muscle strength, propioception-balance and flexibility; and 3. Handing out of at-home exercise chart (twice/week). Main variable: pre-frailty according to the Fried phenotype. Secondary variables: sociodemographic, clinical and functional variables; exercise program adherence, patient satisfaction with the program and quality of life. We will perform an intention-to-treat analysis by comparing the retrogression from pre-frailty (1 or 2 Fried criteria) to robust status (0 Fried criteria) by the end of the intervention, 6 months and 12 months post-intervention. The accumulated incidence in each group will be calculated, as well as the relative risk (RR) and the number needed to treat (NNT) with their corresponding 95% confidence intervals. Protocol was approved by the Ethics Committee Hospital la Paz.

**Discussion:**

Within the context of regular clinical practice, our results will provide evidence regarding the effects of exercise interventions on frailty among pre-frail older adults, a key population given their significant potential for functional, physical, and mental health improvement.

**Trial registration:**

NCT03568084. Registered 26 June 2018. Date of enrollment of the first participant to the trial: July 2nd 2018.

## Background

Worldwide, Spain enjoys one of the highest life expectancies and population projections point to a continuing population ageing process [1].

The 2012 European region committee for The World Health Organization approved the “Strategy and action plan for healthy aging in Europe 2012-2020” [2]. Similarly, the European Union, within the framework program Horizon 2020, launched a program for “the cooperation for innovation in Europe regarding active and healthy ageing.” One of the program’s pillars of action is the prevention, screening, and early diagnosis of frailty and functional deficit [3].

In the context of healthy ageing, the older person stays healthy and remains independent longer thus reducing the family burden in terms of informal care. The opposite scenario is functional decline, i.e., frailty, defined as a decrease in the homeostatic reserve of the individual leading to increased vulnerability to stressors. Frailty is a reliable predictor of short, medium, and longterm adverse health events such as falls, multimorbidity, institutionalization, hospitalization, and even death [4]. Frailty prevention and control is currently an important public health challenge clearly associated to the hastened population ageing.

Frailty and pre-frailty are commonly found among the elderly. A recent systematic review estimates that about 10 and 44% of 65-year-olds or older are frail or pre-frail, respectively [5]. It is worth underlining that the frailty syndrome is reversible, that is, a frail individual can turn the clock back and become robust again as long as frailty is detected and treated at the onset [6]. Therefore, identifying and treating pre-frailty is effective in preventing disability and other adverse events, improving quality of life, and reducing care-related costs [7, 8]. Further, pre-frailty is the most appropriate time to implement interventions by the health care system as it is when the best patient response to these interventions can be expected [9].

Lowering frailty rates requires reducing inactivity, one of its main risk factors [10]. Both a 2012 and a 2014 meta-analysis studying fragile individuals showed that physical activity delays and even reverses frailty and disability [11, 12], improves cognitive status and promotes emotional well-being and socialization [13]. Specifically, multicomponent physical exercise programs comprised of muscle strength development, cardiovascular endurance, and joint mobility and balance, are the most effective interventions to delay disability and other adverse events as well as to maintain the highest degree of independence possible for each individual [14]. However, how different trials measure interventions varies which difficults results comparisons. Therefore, physical activity, insofar as it prevents and even reverses early stages of frailty, has the potential of averting falls, disability, and improving quality of life [15]. Not to be dismissed, mood enhancement and the socialization inherent to group exercise programs may also contribute to these benefits.

Furthermore, physical inactivity is also the primary cause of most chronic pathologies [16]. Therefore, it is of interest to analyze the evolution of the control parameters of these pathologies (especially those related to cardiovascular risk) usually monitored by primary care medical staff, from baseline through the follow-ups while performing physical exercise regularly for any substantial amount of time.

Other interventions such as increasing vitamin D levels, resolving an underlying anemia, or increasing protein intake have shown improvement in the elderly’s physical function, independently from regular exercise’s benefit, and should be implemented within the context of usual clinical practice [17].

In Spain, primary care, is not only the point of entry into the health system but it also provides accessibility to diverse strata of the population with low disease burden. Further, it offers continuity of care along with a comprehensive approach including disease prevention and health promotion [18]. Thus, primary care is ideally positioned to play a crucial role in this intervention program, through the maintenance and improvement of physical, cognitive, and social functioning among the elderly, as well as the promotion of individual self-care for as long as possible.

In addition, primary care is also the default for pre-frail individuals (close to 50% of all elderly) to receive care. Therefore, it is the ideal place for “exercise prescription,” for teaching the necessary skills, and, last but not least, for promoting self-care, participation, and individual empowerment [19]. Consequently, it is primary care’s responsibility to implement this type of program, upon documented evidence of its effectiveness in the context of clinical practice. Unfortunately, this evidence is scarce in Mediterranean countries [13, 20], especially with pre-fragile individuals [21, 22].

Long-term multifactorial interventions have been shown to be more cost-effective than regular clinical practice [9]. However, implementating these programs in clinical practice usually encounters significant barriers thus limiting their effectiveness. These barriers include, among others, inadequate planning and coordination among professionals, insufficient support at the service provider level, inadequate dedication of the personnel involved, and not active enough attitudes on the part of key participants [23, 24].

Adherence to exercise among previously sedentary frail or pre-frail elderly fails to reach even 50% [22], although it is somewhat higher for aerobic exercises such as walking or cycling versus strength exercises, and is also higher for group exercises versus proposed home exercises [25]. An exercise intervention pilot study in frail 65 year-olds and older performed by our team in the Primary Care Health Center Doctor Castroviejo (unpublished data), yielded a 28.3% adherence rate when defining adherence as participation in at least 70% of the sessions. Among the barriers limiting the recruitment and adherence to exercise programs, the more common included already getting enough exercise, not being motivated or ready and having poor health [26].

Currently in Spain, significant lines of research on exercise and healthy ageing are underway, although not of them has involved primary care [27, 28]. In fact and as far as we know, there have been few interventions performed exclusively with pre-frail individuals [21, 22], thus, such studies are needed to provide evidence generalizable to this population [9].

Based on this evidence, this project aims to create a multicomponent physical exercise program for pre-frail individuals. In contrast to previous ones, our project would be nestled within the structure and practice of primary care. We would examine its effectiveness as well as all and every aspect related to the implementation of such a program in the context of primary care.

## Aims

Main goal of the MEFAP-project is to evaluate the effect of a multicomponent physical activity program in the primary care setting, versus regular medical practice, in reversing pre-frailty status [4] 12 months post-intervention among patients over 70 years of age.

Secondary Objectives of the study are:

-To evaluate the effect of MEFAP versus regular medical practice at 0- and 6-months post-intervention regarding: pre-frailty status according to the Fried scale, quality of life, and clinical parameters such as blood pressure, body mass index (BMI), cognitive status, mood and chronic pain, and biological parameters such as metabolic and inflammatory markers.

- Assess adherence to MEFAP and participant satisfaction.

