**Fig. 1 Fig1:**
[figure not shown]
MEFAP Project Design**.** MEFAP: Multicomponent physical activity program (for its acronym in Spanish)

**Table 1 Tab1:** Schedule of enrollment, interventions, and assessments in MEFAP Project

TIMEPOINT	Enrolment	Allocation				End of Study
	*-t* _*1*_	0	*t* _*1 baseline*_	*Intervention*	*t* _*2*_ *6 –months post-intervention*	*t* _*3*_ *12–months post-intervention*
ENROLMENT						
Eligibility screen	X					
Informed consent	X					
Randomized Allocation		X				
INTERVENTION						
INTERVENTION GROUP: *Multicomponent Exercise Program (MEFAP)*				X		
*CONTROL GROUP: Regular Clinical Practice*				X		
ASSESSMENTS						

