***Main outcome variables:***						
*● Frailty level (Fried Criteria)*	X		X		X	X
*Secondary outcome variables*						
*● Function-related variables: SPPB, risk of falls*			X		X	X
*● Quality of life*			X			X
*● Clinical Parameters:*						
✓ Blood pressure			X		X	X
✓ BMI			X		X	X
✓ Cognitive state (MEC30 Lobo)			X		X	X
✓ Mood (Yesavage test)			X		X	X
✓ Chronic-use drugs (last 2 weeks).			X		X	X
✓ Chronic pain						
*● Analytical Parameters (metabolic and inflammation).*					X	X
*● Program adherence and satisfaction level*			X			X
*Independent Variables*						
*● Sociodemographic*			X			
*● Comorbidity o diagnosis of ≥ 2 chronic disease*			X			
*● Fracture in previous 5 years*			X			

*MEFAP:* Multicomponent physical activity program (for its acronym in Spanish), *SPPB* short physical performance battery, *BMI* Body Mass Index, *MEC30 Lobo* Mini-mental Exam Cognitive (Translated and adapted to Spanish by Lobo et al. 2002 [33])

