### Study variables

a) Main Outcome: Change in patient’s frailty level from pre-frail to robust. Frailty status is based on Fried criteria [4]: low gait when walking 4 m, grip strength with the dominant hand measured with a dynamometer, unintentional weight loss > 5% of body weight in the past year, low energy (CES-D) [34], and low physical activity (Yale scale) [35]. Pre-frailty is defined as meeting 1 or 2 Fried criteria and robust status is defined as meeting none (0) of Fried criteria.

b) Secondary outcome variables: Variables related to physical functioning: short physical performance battery (SPPB) [30], risk of falls (measured according to consensus proposal on the prevention of frailty and falls [29]. Quality of life: Measure with the EuroQol questionnaire 5D-5 L [36]. Adherence to the program and degree of satisfaction: Patients will be considered to have a good MEFAP adherence when they have attended at least 75% of the sessions**.** With regard to satisfaction, the dimensions of communication, professional attitude, technical competence and accessibility will be evaluated based on a questionnaire created for this purpose and measured with a Likert scale.

Clinical parameters: blood pressure, BMI, Cognitive state (MEC30 Lobo) [33] mood (Yesavage test) [37], chronic pain, and any chronic drugs consumed in the last two weeks. Analytical parameters: blood count, glucose and glycated hemoglobin, lipid profile, iron metabolism (iron, ferritin, transferrin), vitamin D, vitamin B12, folic acid, total proteins, and albumin and inflammation markers (ESR, CRP and fibrinogen).

c) Independent variables. Sociodemographic**:** age, sex, educational level, economic level (monthly family income in euros), main professional occupation. Clinical: Fracture in the previous five years (specify if hip fracture), Comorbidity or diagnosis of at least 2 diseases from the following list: Heart disease (arrhythmia, heart failure or ischemic heart disease), cerebrovascular disease, diabetes mellitus, chronic lung disease (asthma, COPD or respiratory failure), chronic kidney disease, cancer, and osteoarthritis / limiting arthritis (i.e., affecting activities of daily living).

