### Data collection

Data will be collected using an electronic data collection notebook (eDCN) designed for the study. There are four visits planned: enrolment (-t1) baseline (t1), at 6 months (t2) and at 12 months (t3) of the end of the intervention. The flowchart according to SPIRIT guidelines can be seen in Table 1.

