## Discussion

The main goal of health services, and primary care specifically, is the prevention of morbidity and mortality. To this end, the proposal of the Consensus on the prevention of frailty and falls [29] aims to introduce exercise into the regular routine of the elderly population to prevent and reduce functional decline. Within this framework, the study’s desirable outcome is to encourage the implementation of an exercise intervention tested in the community sphere so physical activity becomes a regular habit in the older adult population. A key characteristic of the study is its pragmatic design of primary care implementation, which not only allows to evaluate the program’s effectiveness but also its feasibility in conditions and settings similar to those where it would be implemented in the future. Therefore, it is also crucial to evaluate aspects such as accessibility to the intervention, adherence to the program, user satisfaction, and increase in quality of life.

The study presents the following limitations: First, there could be confounding effects if those assigned to the CG were to follow the intervention. In order to minimize this possibility and avoid attrition in the CG, these participants will be offered participation in a similar multicomponent exercise program at the end of the study period. Second, we expect a lower participation rate among individuals whose Primary Care Health Center is further away or the corresponding physical therapy center is not easily accessible by private or public transport. This information will become an important data point as social and health services must be highly accessible to the user. Thus, we propose to analyze the relationship between user accessibility (in time, distance and comfort) and adherence to program.

Third, participants will not be blind to group assignment due to the trial’s design. However, outcome evaluation will be conducted by skilled interviewers that are blinded for treatment allocation. The statistician conducting the analysis will neither know to which study group a given patient has been assigned.

One of the main strengths of the study is its pragmatic design placing the program implemention within primary health care, that is, in similar conditions to real-world implementation. This, in turn, may help the prescription of exercise become a therapeutic tool within the comprehensive care of the elderly patient.

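### Quality of life is a secondary objective at 6 months, but Table 1 schedules it only at baseline and 12 months, although a 6-month visit exists

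*Protocol article*

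**What the plan says.** The first secondary objective in the Aims is to compare the programme with regular medical practice "at 0- and 6-months post-intervention regarding: pre-frailty status according to the Fried scale, quality of life", followed by clinical and biological parameters. The instrument is given under Study variables: "Quality of life: Measure with the EuroQol questionnaire 5D-5 L". That section gives no time points.

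The timing comes from Table 1, titled "Schedule of enrollment, interventions, and assessments in MEFAP Project". Its row "Quality of life" is marked at baseline (t1) and at 12 months (t3), and its 6-month cell (t2) is empty. The row just above, "Function-related variables: SPPB, risk of falls", is marked at t1, t2 and t3.

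The Data collection section lists enrolment and baseline visits and then follow-up "at 6 months (t2) and at 12 months (t3) of the end of the intervention". The Discussion calls it crucial to evaluate aspects that include "adherence to the program, user satisfaction, and increase in quality of life".

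**The concern.** An objective and the assessment schedule should name the same times. For quality of life they share none after baseline: the objective names 0 and 6 months, and the schedule supplies 12 months.

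At 6 months this is not for want of a visit. Patients are scheduled to attend t2, and most of the other secondary outcomes are marked there. Quality of life is left off.

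A questionnaire not given at a visit cannot be recovered afterwards, and no analysis plan can compare arms on it. The 12-month score will exist, but the only objective set at 12 months concerns pre-frailty status. A 12-month quality-of-life result would therefore be reported against an objective that does not mention that time. Staff who follow the Aims and staff who follow Table 1 could also collect different data at t2.

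**Working it through.** No sample-size or power figure is involved, so the check sets the objective against the schedule.

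**1. Columns of Table 1.** After the row label there are six: enrolment (-t1), allocation (0), baseline (t1), intervention, 6 months post-intervention (t2) and 12 months post-intervention (t3). The column headed 0 is allocation, not 0 months after the intervention.

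**2. Is the empty cell a text-extraction artefact?** Each of the six rows checked splits into 7 cells (1 label + 6 columns), so the quality-of-life row is not shifted. Four of them, without the label:

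| Row | -t1 | 0 | t1 | Interv. | t2 (6 m) | t3 (12 m) |
|---|---|---|---|---|---|---|
| Frailty level | X | | X | | X | X |
| SPPB, risk of falls | | | X | | X | X |
| Quality of life | | | X | | empty | X |
| Blood pressure | | | X | | X | X |

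BMI, cognitive state and mood show the same pattern as blood pressure.

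**3. Objective against schedule for quality of life.**

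| Time after intervention | In the secondary objective | Visit planned | Marked in Table 1 |
|---|---|---|---|
| 0 months | yes | no, for any outcome | no |
| 6 months | yes | yes (t2) | no |
| 12 months | no | yes (t3) | yes |

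Times in the objective: {0, 6}. Post-baseline times in the schedule: {12}. Overlap: none.

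**4. The two gaps differ in kind.** At 6 months the visit exists and this instrument is missing from it, so the gap is particular to quality of life among the outcomes tabulated above. At 0 months neither Table 1 nor the Data collection section has a visit, so the gap also affects Fried status and the other outcomes, although the Abstract and the Analysis strategy plan results at that point. Adding a 0-month visit would leave the 6-month gap open.

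**5. Size.** If Table 1 is followed, 0 of the 190 planned patients have a 6-month EQ-5D-5L score. Nothing else in the article schedules the questionnaire at 6 months.

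**The case against.** The strongest reply is that Table 1 is a condensed and imperfect table, so one empty cell is weak evidence of what will be done. Other rows look misfilled. Chronic pain has no mark at any visit. Analytical parameters have no baseline mark, although the Intervention section says participants receive their analytical results after the baseline interview. Adherence and satisfaction are marked at baseline, before any session. Figure 1, the full protocol and the electronic data collection form are not at hand, and any of them might show the questionnaire at t2.

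This stands as a limit on certainty. It does not support saying that the questionnaire will not be given at 6 months, only that the schedule as printed leaves it out. It does not remove the contradiction, because the article states both the objective and the schedule and one of them must change. Nor is this detail left to an analysis plan: that plan can only use data that are collected.

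A second reply is that the objective could instead be changed to match Table 1. That would make the text consistent, and 12 months is the time of the main goal, so the 12-month score has value. But it would give up a comparison the authors chose to state, when a visit to collect it already exists.

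Third, only one secondary outcome is involved. That is correct and limits the weight of the point.

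**Conclusion.** The point holds for 6 months. The secondary objective asks for a quality-of-life comparison that Table 1 does not supply, and the 12-month score it does supply lies outside the times in that objective. If Table 1 is followed, the 6-month comparison has no data. The conclusion assumes that Table 1 reflects what sites will do. It should be corrected, but it does not touch the primary outcome, the sample size or the main analysis.

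A reader might infer more than the document supports:

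- **That quality of life alone has been left out at both times in its objective.** At 0 months no outcome has a visit, so that is a separate, general problem.
- **That planned attrition measures the loss.** The 30% allowance in the sample-size section applies to follow-up in general and would be the same with the questionnaire marked at t2. It does mean that not every patient can be assumed to attend t2.
- **That the 12-month result is uninformative because any effect will have faded.** The article gives no figure on how a quality-of-life effect changes over time.

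**What to change.** Mark the EQ-5D-5L at t2 in Table 1, so that it is collected at t1, t2 and t3, and make the data collection form agree. Add 12 months to the quality-of-life objective, so that the score already scheduled at t3 answers a stated question.

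Settle 0 months separately and explicitly. If a 0-month visit is added, give the EQ-5D-5L there too. If not, remove 0 months from the objective openly, in a recorded change, and not by silent rewording.

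The cost is one short questionnaire, already in use at t1 and t3, at an existing visit, plus wording changes. No new patients are needed, and no new visit is needed for the 6-month correction. There is one downside. The Abstract dates the first enrolment to July 2018, so the change may come after some t2 visits have passed. Those patients will lack a 6-month score, and the report should give their number by arm and the date of the change.

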## Methods

### Design and setting

Pragmatic multicenter randomized clinical trial with parallel groups followed for 12 months. The setting is the primary health care of the Spanish national health system. Figure 1 shows the study design which was informed by SPIRIT guidelines, which will also guide the study reporting (Table 1).

